### Masking

2.7

For practical purposes, any research team member who provides or supports the interventions, including the Co-PI, are unmasked. Research team members who conduct pre-and post-intervention assessments, including the study PI, are masked to group assignment with one exception. Research team members who assess anatomy or physiology with instruments like MRI are not necessarily masked, as their knowledge of group membership is unlikely to influence outcomes. These individuals are not involved in data analysis where bias could be introduced. The study PI will only become unmasked in the instance of an adverse event, if the Co-PI is unable to share adequate details with the research compliance office (highly unlikely). Otherwise, the study PI will become unmasked after post-intervention assessments are completed and scored.

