**Methods:**

This study is a single-blind randomized controlled trial comparing group yoga to group low-impact exercise. Participants must be ≥18 years old with chronic ABI and moderate balance impairments. Group yoga and group exercise sessions occur twice a week for 1 h for 8 weeks. Sessions are led by trained adaptive exercise specialists. Primary outcomes are balance and ANS function. Secondary outcomes are brain function and structure, cognition, quality of life, and qualitative experiences. Data analysis for primary and most secondary outcomes will be completed with mixed effect statistical methods to evaluate the within-subject factor of time (i.e., pre vs. post intervention), the between-subject factor of group (yoga vs. low-impact exercise), and interaction effects. Deductive and inductive techniques will be used to analyze qualitative data.

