From the pairs of the DWIs acquired with reversed phase-encoding blips, susceptibility-induced off-resonance field is estimated (Andersson et al., 2003), as implemented in functional magnetic resonance imaging of the Brain Software Library (FSL) as top-up (Smith et al., 2004) generating a single corrected (or unwarped b = 0 image). Then, the top-up distortion correction is applied using eddy in FSL (Andersson and Sotiropoulos, 2016), which also corrects for distortions related to eddy current and motion. The diffusion tensor model can be fitted to the data using the FSL Diffusion Toolbox v.5.0 (FDT), yielding the FA maps. In addition, the NODDI model is fit to the data using NODDI toolbox in Matlab. All steps of image processing and registration are visually inspected. Finally, we use the tract-based spatial statistics (TBSS) (Smith et al., 2007) workflow in FSL v6.0.5.2. In brief, this includes: (a) nonlinear alignment of each participant’s FA volume to the 1 × 1 × 1 mm 3 standard Montreal Neurological Institute (MNI) space via the FMRIB58_FA template using the FMRIB’s Nonlinear Registration Tool (FNIRT, Rueckert et al., 1999),^2^ (b) calculation of the mean of all aligned FA images, (c) and the option to create a WM “skeleton” (a representation of WM tracts common to all subjects) by perpendicular non-maximum-suppression of the mean FA image and setting the FA threshold to 0.2, (d) perpendicular projection of the highest FA value (local center-of-tract) onto the skeleton, separately for each subject. Finally, we apply tbss_non_FA procedure to MWF and NODDI maps aligned with the unwarped b = 0 images, yielding MWF, FISO, and ICVF values projected on the skeleton.

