### Data management

2.11

All data are indexed using participant IDs to promote confidentiality, although the study PI has a list that links study ID to participant names. This list is on a password protected spreadsheet and saved to the PI’s personal network drive on a password protected computer. Raw data for all outcome measures are saved on university network drives, which are regularly backed-up by the IT department. Scored or summarized data are also stored within a Microsoft Access database which is managed by the study PI and the project manager. This database is also located on a university network drive. Most data can be imported into the Microsoft Access database directly from the acquisition program, which reduces the possibility of human error in data entry. Manual data entry is completed by a trained research assistant for participant demographic information including age, sex, race and ethnicity, type of ABI, time since injury, self-reported balance limitation, prescription medication use, and handedness. These data are reviewed by the study PI to ensure accuracy.

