### Data monitoring

2.12

The size of the study and associated budget did not support creation of a data monitoring committee. In addition to careful monitoring of possible adverse events during each yoga or exercise sessions, the study PI is responsible for evaluating all outcome data following post-intervention visits of the first cohort to assess if there are any significant safety concerns or poor outcomes that warrant termination of the trial.

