### Access to data

3.5

The study PI and Co-PI will have direct access to the complete final dataset. Other research team members will be granted access to the complete dataset if they submit a request with scientific merit to the study PI. Otherwise, research team members with certain expertise (e.g., with ANS data analysis) will likely only have access to those specific data to prevent accidental disruption, deletion, or corruption of data files.

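### The PI's unmasking is tied to scoring of assessments, not to frozen data and completed primary models, and the rule does not say whether it means both cohorts

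*Protocol article*

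**What the plan says.** The trial is described as single-blind (Abstract, Methods: "This study is a single-blind randomized controlled trial"). Section 2.7 leaves those who deliver or support the interventions, including the Co-PI, unmasked. Those who assess outcomes, "including the study PI, are masked to group assignment with one exception". The exception is staff who measure anatomy or physiology with instruments such as MRI. They may know the arm, and of them the section says: "These individuals are not involved in data analysis where bias could be introduced".

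For the PI, the section gives an early-unmasking route for adverse events and then the general rule: "Otherwise, the study PI will become unmasked after post-intervention assessments are completed and scored".

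Other sections set out the PI's remaining roles:

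- **2.11 (Data management):** scored or summarised data sit in a "Microsoft Access database which is managed by the study PI and the project manager".
- **3.5 (Access to data):** "The study PI and Co-PI will have direct access to the complete final dataset".
- **2.12 (Data monitoring):** with no monitoring committee, "the study PI is responsible for evaluating all outcome data following post-intervention visits of the first cohort", to judge whether the trial should end.
- **2.9.1.1 (Standing balance):** the PI fits the equipment and stands beside participants during balance testing.

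Under 2.6, the biostatistician made the allocation sequence and shared it with the Co-PI and the project manager.

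**The concern.** Masked assessment protects the measurements. It does not protect decisions made between measurement and result, such as which records are dropped, which outliers are acted on and which metric is analysed next. Section 2.7 recognises this when it reassures the reader about the instrument operators by keeping them out of analysis. For the PI, the same section ends masking at scoring and adds no such exclusion.

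If the PI, or an analyst working with the PI, made such choices knowing the arms, a reader of the results could not rule out that this knowledge shaped them. With 36 planned participants, a handful of exclusions could matter. Section 4.1 states directional expectations favouring yoga for ANS function, neural outcomes, cognition and quality of life, so there is a preferred answer for those outcomes.

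The second issue is the cohort. If the rule applies cohort by cohort, the PI could know the arms and results of Cohort 1 before testing Cohort 2.

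**Working it through.** The plan gives no figure on this point to reproduce, so the check is a comparison of sections, with one subtraction.

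**1. What the unmasking rule requires.** Section 2.7 requires that post-intervention assessments be completed and scored. It does not require frozen signal processing, frozen exclusions, a locked database or fitted primary models. The rule fixes the earliest point of unmasking. It does not fix the order of unmasking and analysis.

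**2. Who is kept out of analysis.** The possibly unmasked MRI and physiology assessors are, by explicit statement in 2.7. No equivalent statement covers the PI after unmasking, or the Co-PI. No section says who runs the primary models or whether that person is masked.

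**3. What the PI can reach.** The PI has the scored-data database (2.11) and the complete final dataset (3.5). The project manager, who co-manages that database, also holds the allocation sequence (2.6). Section 2.11 does not list allocation among the database contents, so the text does not show that the arms are visible there.

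**4. Which choices can still be open after scoring.**

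- 2.13.2: several HRV metrics are available, and LF band power is named for the initial analysis of this primary outcome. What follows it is open.
- 2.14.1 and 2.14.2: the connectivity and structural analyses take their direction from the behavioural results.
- 2.9.2.3: the fNIRS channel-rejection map is consulted for outliers once the group-level analysis has been done.
- 2.15: missing data are handled by removal.

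None of these steps is assigned to the PI. All can fall after the point at which 2.7 allows the PI to be unmasked.

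**5. Which cohort.** Section 2.8 places Cohort 1 in spring 2023 and Cohort 2 in fall 2023. Section 2.6 gives 12 recruits in Cohort 1, and section 2.5 gives a revised planned total of 36.

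- Planned for Cohort 2: 36 − 12 = 24
- Share of the planned sample: 24 / 36 = 0.67

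Under the both-cohorts reading, every assessment by the PI is masked. Under the cohort-by-cohort reading, the PI could be unmasked to Cohort 1 before about two thirds of the planned sample is assessed. The PI would still not know the individual assignments in Cohort 2, because its sequence is generated separately (2.6), but would know how the arms had fared. Section 2.12 has the PI review all outcome data at exactly this point and does not say whether the review is masked. The text does not settle which reading is meant.

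**The case against.** The strongest reply is that nothing promised has been broken. A single-blind trial with masked assessors does not promise masked analysts, and unmasking after scoring keeps that promise. The sentence about bias in analysis concerns staff who may know the arm while measuring. The PI measures masked, which is a different case. That stands: the two statements in 2.7 differ in rigour but do not contradict each other.

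A reader might infer that the PI runs the analysis, or that the PI must be unmasked before the models are fitted. Neither is stated. A biostatistician is named in 2.6, and the rule gives only an earliest point.

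A reader might also take the sentence "All steps of image processing and registration are visually inspected" (2.9.2.1) as an unmasked judgement by the PI. The text does not assign that step to the PI or place it after scoring.

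A reader might want to put an inflated false-positive rate on the problem. The obvious calculation, the chance that the smallest of several two-sided p-values falls below 0.05, does not measure it. Swapping the arm labels leaves every two-sided p-value unchanged, so the rate is the same with coded arms. It measures selection among metrics, not unmasking.

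Nor does bias toward the stated hypothesis always mean bias toward a yoga effect. For balance, on which the trial is powered, section 4.1.1 predicts no difference between groups.

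Finally, masking of analysts is often left to an analysis plan, which is not shown here. Its absence from the article would be no finding. The point rests on the timing rule that the article does state, and on the unspecified cohort within it.

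**Conclusion.** The point holds as a minor improvement to a stated rule. Section 2.7 ends the PI's masking at scoring, does not tie it to frozen data or completed primary models, and leaves open whether both cohorts must be finished. Together with the PI's roles in 2.11, 2.12 and 3.5, this permits unmasked analytic choices after scoring and, on one reading, unmasking before 24 of the 36 planned participants are assessed.

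The documents do not show that either will happen, and the size of any bias cannot be computed from them. The 24 assumes that Cohort 1 closed at 12 and that the revised target of 36 is met. Exposure is limited for the primary measurements, which are instrumented. It is greater for the follow-on HRV, imaging and fNIRS analyses, where the choices are open.

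**What to change.** In 2.7, replace the unmasking sentence with a rule that the PI and whoever runs the analysis stay masked until three conditions are met:

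1. Post-intervention assessments of both cohorts are scored.
2. Quality exclusions are frozen.
3. The primary balance and LF-power models have been run with arms coded A/B by the biostatistician.

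The adverse-event exception stays as it is. The Cohort 1 review in 2.12 would then be done without arm identities unless that exception applies.

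The Co-PI and project manager already hold the sequence, so the biostatistician cannot be the only holder of the key. Add that these two take no part in decisions on exclusions or models before that point. In 2.11 and 3.5, add that allocation information, and session records that reveal it, are kept apart from the analysis dataset.

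The cost is a few sentences, a later date at which the PI learns the arms, and some separation of access. Because the project manager co-manages the database and holds the sequence, that separation needs a small practical arrangement. No change to enrolment, assessments or interventions is required.

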### Interventions

2.8

Each intervention consists of 1-h sessions occurring twice per week for 8 weeks, for 16 total sessions. Interventions are delivered in classrooms within the same university building at the same time of day and day of the week. For this study, interventions are delivered in two cohorts. Specifically, up to 12 participants complete adaptive group yoga, and up to 12 participants complete low-impact group exercise in the first cohort, which occurs in the spring of 2023. Likewise, up to 12 participants complete adaptive group yoga, and 12 participants complete low-impact exercise in the second cohort, which occurs in the fall of 2023. In previous work, we have found that class sizes up to 12 participants is optimal for participant engagement and safety; thus, a cohort design was selected to reach enrollment numbers while ensuring participant safety. All study components, especially interventions, are delivered as similarly as possible from the same interventionists, so that participants from the two cohorts can be combined for analyses.

#### Adaptive group yoga (active)

2.8.1

Hatha yoga is considered the foundation of yoga in the west and was used in both feasibility studies (Stephens et al., 2020, 2023). As in prior studies, yoga is delivered in a standardized progression using an established, manualized protocol. Sessions include breath work (pranayama), gentle stretching and holding of postures (asanas), mantra (repeated words), and meditation (dhyana); (see Stephens et al., 2023; Supplementary Table S1 for protocol details). Modifications are incorporated so all participants can successfully complete yoga sessions. During yoga sessions, the interventionist supports performance by modifying poses as appropriate, providing hands-on assistance to help participants move through poses, and using chairs/props to allow participants to complete postures.

#### Low-impact group exercise (control)

2.8.2

The low-intensity exercise control group is matched to the estimated metabolic costs of yoga, 2.5 Metabolic Equivalent of Task (MET; Ainsworth et al., 2011). The exercise sessions were designed by members of the research team with significant experience in exercise protocol development (Leach et al., 2023), and included warm up, cool down, and five, 10-min exercise stations, (e.g., walking, balance, resistance bands, weight-bearing exercise, and core work); (see Leach et al., 2023 for protocol details). Exercise intensity was between 2.0 and 3.0 METs, equating to 30–40% heart rate reserve, and rating of perceived exertion (RPE) of 1–3, which represents light intensity (American College of Sports Medicine, 2017). Like the yoga intervention, exercise is delivered using an established manualized protocol. Heart rate zones are calculated for each participant and monitored along with RPE during exercise sessions to ensure fidelity to the prescribed intensity.

#### Additional procedures for both interventions

2.8.3

All participants are informed that they can discontinue yoga or low-impact exercise at any time. In prior work (Stephens et al., 2020, 2022), there have been no adverse effects from yoga, but the research team is carefully monitoring participants at each yoga or exercise session for any adverse event, such as falls, fainting episodes, or significant discomfort. As noted, both interventions have manualized protocols to guide sessions to ensure adherence to the protocols. Additionally, adherence is being monitored for each yoga and exercise sessions with fidelity checklists. The Co-PI, who is not a masked assessor, reviews checklists throughout the intervention period, and – if necessary – meeting with interventionists to improve protocol adherence. Fidelity metrics are also being tracked for both interventions and will be reported with study outcomes. Finally, because participants are in a chronic phase of acquired brain injury recovery, they are rarely receiving concomitant care or other interventions. However, participants are asked to disclose concomitant care, interventions, or exercise protocols they might be following during the intervention period, but they are not prohibited from continuing with these activities.

### Outcome measures

2.9

#### Primary outcomes

2.9.1

Primary outcome data are acquired at pre-intervention and post-intervention assessments, and measures used to evaluate HRV are acquired throughout both interventions. Pre-intervention assessments are scheduled 2–3 weeks before start of yoga or exercise sessions, and post-intervention assessments are scheduled within 2 weeks of the last yoga or exercise session. See Figure 1 for additional detail on the participant timeline.

##### Standing balance

2.9.1.1

Balance performance is assessed using two methods:Balance is first assessed using a validated measure (Peller et al., 2023), the National Institutes of Health (NIH) Toolbox Standing Balance Task. This measure is administered using the NIH Toolbox app on an iPad (version 9) and the Balance Pod app on an iPhone (version 6), which are paired via Bluetooth. Prior to data acquisition, the study PI places a gait belt on the participant and secures the iPhone to the gait belt using a cellphone armband that is affixed to the gait belt. The Balance Pod app, via the iPhone, measures anterior–posterior sway during balance tasks which include: bipedal standing on a hard surface with eyes open; bipedal standing on a hard surface with eyes closed; bipedal standing on a soft surface (foam pad) with eyes open; bipedal standing on a soft surface with eyes closed; and tandem standing on a hard surface with eyes open. For all balance tasks, participants must remove their shoes and place their feet together with their heels and balls of feet touching. For eyes-open tasks, participants are instructed to fixate on an ‘X’ which is placed on wall in front of them at shoulder height. Tasks are administered in order of difficulty, starting with the easiest task (bipedal standing on a hard surface with eyes open). Each task lasts 50 s and can be repeated once if the participant has loss of balance (LOB) and steps out of the position. For safety purposes, participants complete all balance tasks in a corner, so they have walls on two sides if LOB occurs. The study PI also stands on their other side to stabilize participants in case of LOB. Only participants who make it to the fifth (and hardest task) complete the second balance assessment method.Balance performance is also assessed using a previously validated (O'Connor et al., 2016; Goble et al., 2018; Richmond et al., 2018) force plate (Balance Tracking Systems, Inc., San Diego, CA) during simultaneous neuroimaging assessment with functional near-infrared spectroscopy (fNIRS). Four balance tasks are administered and include: bipedal standing on a hard surface with eyes open; bipedal standing on a hard surface with eyes closed; bipedal standing on a soft surface (foam pad) with eyes open; and bipedal standing on a soft surface with eyes closed. Each task is 30 s in duration, and tasks are repeated four times for a total of 16 trials, as task repetition is necessary to generate an averaged brain response. Balance performance for each trial is acquired with a sampling frequency of 25 Hz, and postural stability is quantified by measuring total center of pressure (COP) length, anterior–posterior COP length, and medio-lateral COP length. Again, for safety purposes, all balance trials are completed in a corner, and the study PI stands near the participant to stabilize them in instances of LOB. A masked study team member documents all instances of LOB during trials.

##### Autonomic nervous system function

2.9.1.2

ANS function is also evaluated using two methods:Prior to the start of the yoga and control exercise sessions, ANS function is evaluated using raw electrocardiogram (ECG) signals which are converted to HRV metrics (see statistical analysis section). Data are acquired at pre-intervention and post-intervention visits within a research lab and during yoga and control exercise sessions. In the research lab, study participants are situated on a medical bed, in a comfortable, semi-recumbent posture in a temperature-controlled (20–22 degrees Celsius), dimly lit room. During 11-min of metronome paced-breathing (6 breaths per minute) raw ECG signals, monitored via a physiological monitor (IntelliVue MP5 Patient Monitor, Philips Healthcare, United States), are recorded using a portable personal computer in conjunction with an analogue-to-digital convertor (WinDaq, Dataq Instruments Inc., Akron, Ohio, USA; Paxton et al., 2011; Williams et al., 2021).During yoga and control exercise sessions, participants wear a Polar H9 chest strap and Unite watch^1^ to acquire and receive ECG signals; these signals are – like data acquired in the research lab – converted to HRV metrics offline after the raw ECG data are downloaded from the Polar cloud (footnote 1). Polar devices have been validated for HRV evaluation (Hernando et al., 2018) and considered the most accurate, commercially available HRV monitors (Stone et al., 2021).

ECG signals collected in the research lab and during yoga and exercise sessions via Polar devices are processed and analyzed offline using commercially available software (Kubios HRV; Tarvainen et al., 2014), as previously described (Tarvainen et al., 2002, 2014). The first 60-s are considered habituation while the study participant becomes accustomed to paced breathing; these data will be discarded from the final analysis.

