Specifically, our team is now conducting a single-blind pilot randomized control trial comparing two intervention arms: 8-weeks of group yoga and 8-weeks of low-impact group exercise in adults with chronic acquired brain injury. All prior studies (Grimm et al., 2017; Stephens et al., 2020, 2023) have been conducted as single-arm yoga intervention studies where participants served as their own controls, and baseline assessments were conducted before no-contact waiting periods and/or the intervention. Therefore, it is possible that the positive outcomes we have reported could be exclusively attributed to well-established benefits of physical exercise or social interaction. In order to determine if yoga has a distinctive impact on functional outcomes, like balance and ANS function, it is necessary to include a control group that mirrors many of the features of the yoga intervention, but lacks unique features of yoga (e.g., breath-to-movement connection). Thus, adding a low-impact group exercise control (Leach et al., 2023) is an essential next step to evaluate if yoga has a unique benefit for adults with chronic ABI. Again, our primary outcome measures are designed to evaluate balance performance and heart rate variability (HRV), as an indicator of ANS function. Secondary outcome measures are designed to: (1) measure neural underpinnings of functional improvements, specifically - functional and structural connectivity of neural networks and task-dependent neural activation during balance tasks and (2) evaluate previously observed outcomes of cognition, quality of life, and qualitative experiences. The overarching purpose of this manuscript is to describe, in detail, all components of our trial protocol to support transparency and replication of methods.

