#### HRV data

2.13.2

There are multiple HRV metrics (e.g., time-series and frequency-band values) calculated within Kubios (Tarvainen et al., 2014). However, a review study showed consistent stabilization of the low frequency (LF) band power after yoga, reflecting an improved equilibrium of parasympathetic and sympathetic activity, (Zou et al., 2018) so initial analyses will use mixed effects statistical model to assess prospective within-subject (factor of time) and between group (yoga vs. control) differences in LF band power data.

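### LF power recorded under 6 breaths/min pacing contains the breathing-driven heart-rate oscillation, so it cannot by itself be read as sympathetic/parasympathetic equilibrium

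*Protocol article*

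**What the plan says.** Autonomic function is one of the two primary outcomes, with "heart rate variability (HRV), as an indicator of ANS function" (Introduction). Section 2.9.1.2 sets the lab conditions: "During 11-min of metronome paced-breathing (6 breaths per minute) raw ECG signals". The opening minute is dropped: "The first 60-s are considered habituation while the study participant becomes accustomed to paced breathing". No unpaced lab recording is described.

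Section 2.13.2 notes that Kubios yields several HRV metrics, then selects one for the initial analyses. It cites a review as showing "consistent stabilization of the low frequency (LF) band power after yoga, reflecting an improved equilibrium of parasympathetic and sympathetic activity", and the mixed model will assess "within-subject (factor of time) and between group (yoga vs. control) differences in LF band power data". No other HRV metric is named for analysis.

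On recordings made outside the lab, section 2.9.1 adds that "measures used to evaluate HRV are acquired throughout both interventions". The yoga arm practises controlled breathing ("Sessions include breath work (pranayama", section 2.8.1). The Introduction describes the comparator as one that "lacks unique features of yoga (e.g., breath-to-movement connection".

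Section 4.1.1 predicts no between-group difference in balance, but a larger improvement in autonomic function with yoga.

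**The concern.** Two stated choices do not fit together: the breathing rate imposed in the lab, and the meaning given to LF power. Breathing makes heart rate oscillate at the breathing frequency. At an ordinary resting rate that oscillation falls above the LF band. At 6 breaths/min it falls inside it, so LF power mixes respiratory variability with whatever else is in the band.

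This matters because autonomic function is the only primary outcome on which yoga is expected to beat exercise. If LF power differs between arms at the post-intervention visit, section 2.13.2 would have the result reported as better autonomic equilibrium. The recording could not separate that from a change in how participants carry out or respond to the paced task. Pacing fixes the rate of breathing but not its depth, and only one arm spends 8 weeks on breath work.

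The direction is also loose. The cited effect is stabilization, and section 4.1.1 speaks of improvement without saying whether LF power should rise or fall. The Introduction describes the dysfunction as sympathetic over-activity, which might suggest a fall. A larger respiratory oscillation under this pacing would produce a rise.

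**Working it through.** The protocol gives no figure to reproduce on this point. The check has four steps.

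**1. Where the paced rate falls.** Inputs from section 2.9.1.2: 6 breaths/min, 11 min recorded, first 60 s discarded.

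- Breathing frequency: 6/60 = 0.10 Hz.
- Analysed segment: 11 × 60 − 60 = 600 s, or 10 min. At 6 breaths/min that is 60 breaths, all paced.

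The LF limits are an assumption. The conventional band and three alternatives were tried:

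| Assumed LF band (Hz) | In breaths/min (× 60) | Contains 0.10 Hz? |
|---|---|---|
| 0.04–0.15 | 2.4–9.0 | yes |
| 0.05–0.15 | 3.0–9.0 | yes |
| 0.04–0.12 | 2.4–7.2 | yes |
| 0.07–0.14 | 4.2–8.4 | yes |

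**2. How much LF power breathing could supply.** This is an illustration on assumed inputs. A 600 s heart-period series sampled at 4 Hz was simulated with a fixed non-respiratory LF component (SD 20 ms) and a respiratory oscillation of amplitude A. LF power was taken over 0.04–0.15 Hz from a Welch spectrum and averaged over 40 runs. As a rough guide, an oscillation of amplitude A inside the band adds about A²/2: 200, 800 and 1800 ms² for A = 20, 40 and 60 ms.

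| A (ms) | LF power at 6 breaths/min (ms²) | Share from breathing |
|---|---|---|
| 0 | 379 | – |
| 20 | 580 | (580 − 379)/580 = 35% |
| 40 | 1134 | (1134 − 379)/1134 = 67% |
| 60 | 2215 | (2215 − 379)/2215 = 83% |

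LF power rises 2215/379 = 5.8-fold through A alone, with the non-respiratory component unchanged. With A = 40 ms, moving the breathing rate from 6 to 15 breaths/min takes LF power from 1134 to 382 ms², almost the value with no respiratory oscillation.

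**3. Which recordings enter the model.** The abstract defines the time factor as pre versus post intervention. Section 2.9.1 places primary data collection at those two assessments and then adds the in-session recordings. Section 2.13.2 does not say that session data enter the LF model. The natural reading is that the lab recordings are analysed, but the protocol does not say so outright.

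**4. Whether a time-domain metric avoids the problem.** An oscillation of amplitude A at frequency f adds √2 · A · sin(π · f · RR) to RMSSD, in quadrature. Assume RR = 0.9 s and a non-respiratory RMSSD of 25 ms, with f = 0.10 Hz:

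- A = 40 ms: √2 × 40 × sin(0.283) = 15.8 ms; total √(25² + 15.8²) = 29.6 ms.
- A = 60 ms: √2 × 60 × sin(0.283) = 23.7 ms; total √(25² + 23.7²) = 34.4 ms.

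RMSSD therefore rises 34.4/25 = 1.4-fold at A = 60 ms. LF power is a squared quantity, so the matching figure on an amplitude scale is √5.8 = 2.4-fold. RMSSD is less exposed to the pacing but not free of it.

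**The case against.** The best defence is that paced breathing is a deliberate standardisation. Rate, posture, room and the discarded minute are the same for both arms and both visits, so the prescribed conditions cannot create an arm difference. The heart-rate response to a fixed breathing stimulus is itself autonomically mediated, so the recording does measure autonomic function. The Introduction also proposes breath work as the mechanism, so an effect through breathing is not foreign to the hypothesis. All of this stands. It limits the point to the label put on LF power; the lab comparison remains valid as a comparison.

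Three stronger readings are tempting, and the protocol does not support them.

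- A reader might infer that LF power here reflects breathing instead of autonomic function, or mainly breathing. The share depends on amplitudes that the protocol does not give. At 20 ms breathing is the minority, and the response to breathing is partly what an autonomic test measures.
- A reader might infer that the lab contrast is biased because yoga participants will breathe more deeply. That is possible, since depth is not controlled, but nothing in the protocol shows it.
- A reader might infer that the in-session recordings build an arm difference into the primary test. Section 2.13.2 does not put them in the model, no session breathing rates are given, and breath work is one of several yoga components.

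It can also be said that LF power is named only for initial analyses and that the choice of metric and sign may be left to an analysis plan not shown. That is fair for the finer detail. It does not answer the point, because the pacing, the metric and the equilibrium reading are all stated here, and it is their combination that fails.

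**Conclusion.** The point holds as one of interpretation. The whole analysed lab recording is paced at 0.10 Hz, which lies in the LF band under all four sets of limits tried. LF power from that recording contains the breathing-driven oscillation and cannot by itself support the equilibrium statement in section 2.13.2. The breathing share was about 35% to 83% in the simulation. Those figures rest on assumed amplitudes and an assumed non-respiratory component, and should be taken as a range of what is possible and not as an estimate for this trial.

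No bias in the lab contrast is demonstrated. What is at risk is the wording of the conclusion on the one primary hypothesis that expects an arm difference. It is worth correcting before the data are analysed, because doing so changes what the trial may claim and needs no new measurement.

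**What to change.** In section 2.13.2:

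1. Define the primary measure as LF power from the pre- and post-intervention lab recordings, described as the heart-rate variability response to paced breathing at 6 breaths/min. State the LF limits used.
2. Remove the interpretation of LF power as sympathetic/parasympathetic equilibrium.
3. State in advance whether a rise or a fall counts as improvement.
4. Report one time-domain metric that Kubios already produces, for example log RMSSD, as supportive. Note that it is less sensitive to the pacing but still affected by it. Making it primary would be a debatable trade, since it reduces the problem without removing it.
5. State that the in-session Polar recordings, made while only one arm does breath work, are process data outside the between-arm primary test.

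The cost is a few sentences of analysis and interpretation text; the same recordings are used. The downside is a narrower autonomic claim and a less direct comparison with the cited review of LF power.
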